## Abstract

**Background:**

Despite administration of annual influenza vaccination, influenza-associated complications in transplant recipients continue to be an important cause of hospitalization and death. Although influenza vaccination has been proven to be the most effective measure to reduce influenza infection after transplantation, transplant recipients are still vulnerable to influenza infections, with lower serological responses to vaccination compared to the general population. In order to assess the efficacy and safety of an alternative immunization scheme for solid organ transplant recipients, the TRANSGRIPE1-2 Study Group aimed to test a booster dose administration 5 weeks after the standard vaccination. The primary objective of this trial was to compare short-term and long-term neutralizing antibody immunogenicity of a booster dose of influenza vaccination to the standard single-dose immunization scheme. Secondary objectives included the evaluation of the efficacy and/or safety, cellular immune response, incidence of influenza infection, graft rejection, retransplant and mortality rates.

**Methods/Design:**

This phase III, randomized, controlled, open-label clinical trial was conducted between October 2012 and December 2013 in 12 Spanish public referral hospitals. Solid organ transplant recipients (liver, kidney, heart or lung), older than 16 years of age more than 30 days after transplantation were eligible to participate. Patients (*N* = 514) were stratified 1:1 by center, type of organ and time after transplantation and who either received the standard single dose (*n* = 257) or were treated according to a novel influenza vaccination schedule comprising the administration of a booster dose 5 weeks after standard vaccination (*n* = 254). Seroconversion rates were measured as a determinant of protection against influenza (main outcome). Efficacy and safety outcomes were followed until 1 year after influenza vaccination with assessment of short-term (0, 5, 10 and 15 weeks) and long-term (12 months) results. Intention-to-treat, per-protocol and safety analyses will be performed.

**Discussion:**

This trial will increase knowledge about the safety and efficacy of a booster dose of influenza vaccine in solid organ transplant recipients. At the time the manuscript was submitted for publication, trial recruitment was closed with a total of 499 participants included during a 2-month period (within the seasonal influenza vaccination campaign).

**Trial registration:**

ClinicalTrials.gov Identifier: NCT01761435 (registered 13 December 2012).

EudraCT Identifier: 2011-003243-21 (registered 4 July 2011).

## Background

Influenza is a contagious, acute, usually self-limited febrile illness caused by infection with influenza A or B virus that occurs during variable severity outbreaks every winter. Solid organ transplant (SOT) recipients have been reported to be more susceptible to influenza virus
[1, 2] compared to the general population. Notwithstanding current vaccination protocols, influenza-associated morbidity and mortality continue to be an important cause of hospitalization and death in SOT recipients
[3, 4]. Influenza infection in this group of patients is associated with significant short-term and long-term complications, such as pneumonia, long viral shedding, graft rejection and death
[3, 5–9]. Thus, efforts are needed to reduce the incidence of influenza in this especially vulnerable population.

One of the most effective proven measures to reduce the incidence and complications of influenza infection is seasonal influenza vaccination. This strategy has been shown to reduce the risk of graft rejection and death during the first year after transplantation
[10]. Although the results of some studies are discordant
[11–20], decreased serological responses to influenza vaccination in SOT recipients, compared to the general population, have been reported in most studies.

Despite increasing vaccine coverage throughout the 2010–2011 influenza season, rates of influenza-associated mortality (7.2%) and ICU hospitalization (16.2%) in SOT recipients remained high
[21]. Several strategies have been evaluated to improve the efficacy of vaccination in SOT recipients, including the use of higher doses of antigen, administration of adjuvanted vaccines and intradermal route of administration
[19, 22–26]. However, these strategies have been assessed only in small cohorts; thus, no clear recommendation can be provided at this time.

Detectable antibody titers against influenza at baseline have been associated with higher postvaccination antibody responses
[15, 20]. However, an annual influenza vaccination to maintain baseline antibody titers that may boost yearly vaccine efficacy may not be sufficient in SOT recipients, because only 30% of SOT recipients maintain detectable neutralizing antibody titers 1 year after vaccination
[27]. This may be due either to immunosuppressive regimens that, although critical for preventing acute rejection, deplete the adaptive arm of the immune system, or to seasonal vaccine strain modifications that may decrease immunogenicity. A booster dose given some weeks after the standard dose may elicit a long-lasting antibody response, thus producing better protection in current and subsequent influenza seasons. The booster strategy has been tested in several studies involving different types of transplant recipients, but the results are as yet inconclusive
[28]. In addition, no randomized controlled trial has addressed this issue to date.

The TRANSGRIPE 1-2 study is a publicly funded, phase III, parallel-group, randomized clinical trial for the evaluation of the safety and efficacy of a booster dose of trivalent inactivated seasonal influenza vaccine administered 5 weeks after seasonal influenza vaccination compared to a single dose of the vaccine administered to SOT recipients. In the present study, we hypothesized that the efficacy of seasonal trivalent inactivated influenza vaccination might be significantly increased in SOT recipients by administering a second booster dose 5 weeks after the standard single-dose vaccination.

The primary objective of the present clinical trial is to compare short-term immunogenicity by measuring neutralizing antibodies after a booster dose versus a standard single dose of influenza vaccine in SOT recipients.

The following are the secondary objectives of the trial:

To compare the long-term immunogenicity of two doses versus a standard single-dose of influenza vaccineTo compare short-term and long-term influenza-specific T-cell immune responses among patients within both treatment armsTo determine the clinical effectiveness of the experimental vaccination scheme, measuring the incidence of confirmed influenza infectionTo establish a safety intervention by analyzing incidence of adverse events (AEs), mortality and outcomes such as graft rejection

Moreover, TRANSGRIPE1-2 trial bears two associated biological substudies in patients who provided specific consent for additional investigations.

## Methods/Design

The TRANSGRIPE1-2 study is a phase III, randomized, controlled, open-label, multicenter clinical trial designed to assess the safety and efficacy of a booster dose of influenza vaccine in SOT outpatients. The study was performed in 12 Spanish referral hospitals between October 2012 and December 2013. The coordinating center was Virgen del Rocío University Hospital, which was responsible for handling clinical trial administrative authorization and regulatory affairs, providing study supplies, independent data and safety monitoring and centralized laboratory immunological quantifications, as well as general coordination and daily operational management of the trial for all of the participating sites. The study was authorized by the Spanish Regulatory Authority and the Coordinating Institutional Review Board of Biomedical Research in Andalusia (Acting as Research Ethics Committee of reference), which gathered the approval from the local ethics committees at all of the participating sites: Virgen del Rocío University Hospital Institutional Review Board (IRB), Seville; Reina Sofía University Hospital IRB, Córdoba; 12 de Octubre University Hospital IRB, Madrid; Gregorio Marañón General University Hospital IRB, Madrid; Ramón y Cajal University Hospital IRB, Madrid; Vall d’Hebron Hospital IRB, Barcelona; Bellvitge University Hospital IRB, Barcelona; Barcelona Clinic Hospital IRB, Barcelona; Cruces University Hospital IRB, San Vicente de Barakaldo; La Fe University Hospital IRB, Valencia; Virgen Macarena University Hospital IRB, Seville; and Marqués de Valdecillas University Hospital IRB, Santander.

### Selection and enrollment

The criteria for patient eligibility are detailed in Table 
1. Before the 2012–2013 flu vaccination campaign started, patients were selected from the local SOT recipients lists and invited to participate. Patients who met the selection criteria and agreed to participate in the clinical trial by signing an informed consent form were randomly assigned to the intervention group and subjected to the study protocol, including baseline extraction of blood samples (prior to the administration of standard single-dose influenza vaccination) for the quantification of baseline cellular and humoral immune response.

**Table 1 Tab1:** **Inclusion and exclusion criteria**

Inclusion criteria	Exclusion criteria
Solid organ transplant recipient (liver, kidney, heart or lung)	Acute graft rejection within 15 days before selection
Age ≥16 years	Documented allergy and/or previous intolerance and/or contraindication to active compounds or excipients or any traces and/or residues in the vaccine
At least 30 days posttransplant	Previous medical record of any severe and/or life-threatening adverse reaction to the vaccine (such as Guillain-Barré syndrome)
Signed informed consent form	Confirmed pregnancy

### Randomization

By 1:1 randomization, patients were allocated either to receive the standard single-dose regimen or to be treated according to a novel influenza vaccination schedule comprising the administration of a booster dose 5 weeks after the first vaccination dose. In order to avoid bias due to differences in immunosuppression level of patients between treatment arms, randomization was stratified according to study sites (because local immunization protocols may differ for SOT recipients), type of organ and time since transplantation. Randomization was centralized and computer-generated, with allocation concealed by integrating a locked list into an electronic case report form (eCRF). A copy of the randomization list is guarded in an opaque, sealed envelope by the trial’s Central Management Team (CMT)at the coordination center that is independent from the investigators who recruited patients.

### Trial intervention and control

Trivalent inactivated influenza vaccine containing World Health Organization–recommended strains for the Northern Hemisphere for the 2012–2013 season was administered. The strains selected for inclusion in the 2012–2013 flu vaccines were an A/California/7/2009(H1N1)pdm09-like virus, an A/Victoria/361/2011(H3N2)-like virus and a B/Wisconsin/1/2010-like virus. The vaccination scheme administered in the two treatment arms is detailed in Table 
2: standard intramuscular influenza vaccination (treatment arm A) versus standard vaccination followed by a second booster dose of the same vaccine 5 weeks apart (treatment arm B).

**Table 2 Tab2:** **Treatment arms**

Treatment arm	Description
Standard influenza vaccination (treatment arm A)	Single intramuscular 0.5-ml dose of inactivated influenza vaccine (split virion) containing World Health Organization (WHO)–recommended strains in Northern Hemisphere and European Union (EU) decision for the 2012–2013 season (A/California/7/2009(H1N1)pdm09-like, A/Victoria/361/2011-like and B/Wisconsin/1/2010-like strains, derived from B/Hubei- Wujiagang/158/2009)
Booster double-dose influenza vaccination (treatment arm B)	Single standard intramuscular 0.5-ml dose of inactivated influenza vaccine (split virion), followed by a second booster dose of the same vaccine 5 weeks later;vaccine strain used was in compliance with the WHO recommendations in Northern Hemisphere and EU decision for the 2012–2013 season (A/California/7/2009(H1N1)pdm09-, A/Victoria/361/2011- and B/Wisconsin/1/2010-like strains, derived from B/Hubei- Wujiagang/158/2009)

The vaccine used for the trial was provided by the Andalusian Health Service, and the pharmacy service of the sponsor’s center was responsible for relabeling and distributing the investigational medicinal product (IMP), according to good manufacturing practices, after obtaining necessary regulatory approval.

Despite the open-label design of the study, all immunologic assays were carried out on coded and anonymous specimens, and data analysts were blinded of which intervention each patient received. During the study period, patients received medical care based on existing local protocols for transplant recipients. Any concomitant medication recommended by clinical practice was allowed within the clinical trial and was registered in the study’s eCRF.

### Follow-up protocol

Patients were followed up at the planned visits by clinical teams at the participating centers, ensuring that essential data about efficacy and safety were registered, and samples were collected (Figure 
1). The duration of the trial was 14 months: 2 months for patient recruitment and 12 months of follow-up. Clinical, analytical and exploratory data needed for the study were collected and logged in the study’s eCRF at each follow-up visit. For immunogenicity studies, patients’ blood samples were collected at baseline prior to vaccination and at each programmed visit after vaccination. Vaccine efficacy was evaluated at baseline, midterm (5, 10 and 15 weeks after immunization) and long-term (12 months after immunization).

**Figure 1 Fig1:**
[figure not shown]
**TRANSGRIPE 1-2 trial design and procedures.** Clinical trial visits are structured in five (or six) time points: initial screening baseline evaluation and administration of the first dose of vaccine in arms A and B (visit 1 and 2), administration in arm B of second dose of vaccine 5 weeks after inclusion (visit 3), short-term follow-up 10 weeks after inclusion (visit 4) and 15 weeks after inclusion (visit 5), as well as long-term follow-up 12 months after the first dose of vaccine (visit 6). Immunogenicity and drug safety were assessed at each programmed time point.

Neutralizing antibody levels for the three influenza strains were measured using microneutralization assays, and seroconversion rates were calculated. Influenza-specific T-cell immune response was measured as the percentage of CD4+ and CD8+ T cells secreting interferon γ in response to influenza stimulation normalized to the negative control.

Clinical trial visits were structured in five (or six) time points as follows:

*Visits 1 and 2*: Patient screening, baseline evaluation and administration of the first dose of vaccine (arms A and B). Protocols for visits 1 and 2 were carried out in one visit when necessary.*Visit 3*: Five weeks after inclusion (range, 25 to 45 days) and administration of the second dose of vaccine (arm B).*Visit 4*: Ten weeks after inclusion (range, 60 to 80 days).*Visit 5*: Fifteen weeks after inclusion (range, 95 to 115 days).*Visit 6*: Twelve months after inclusion (range, 11 to 13 months).

In the programmed visits, patients were prompted to notify the clinician of the onset or continuation of symptoms related to influenza infection occurring during the follow-up period or by email or telephone if symptoms arose during the period between visits. In cases of symptoms, a nasopharyngeal swab was taken for detection of influenza infection using RT-PCR assays.

Each participant had the right to withdraw consent from the study at any point according to international rules. Furthermore, a participant was removed from the study at any time if any of the following withdrawal criteria were met: noncompliance with study procedures and requirements, such as not attending at least two consecutive visits, or if clinical circumstances (for example, AEs, comorbidities) required discontinuation of the study medication or follow-up procedures according to an investigator’s judgment. Patients who left the study fulfilled the study procedure of premature finalization, and AEs were followed until resolution. Statistical analysis was carried out for all the patients who received the first dose of influenza vaccine.

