**Table 3 Tab3:** **Study variables**
^**a**^

Category	Variables
Demographic data	Sex and age
Comorbidities	COPD, diabetes, obesity, kidney failure, hepatic disease, AIDS, cancer, leukemia, connective tissue disease, cerebrovascular disease, other comorbidities
Previous vaccinations	Influenza vaccination (seasons 2011–2012 and 2010–2011), influenza A H1N1 (2009) vaccination, pneumococcal conjugate vaccination, other immunizations
Solid organ Transplant	Date, organ, immunosuppressive treatment, graft rejection history, use of monoclonal antibodies
Influenza infection records	Confirmed influenza infection in previous season, confirmed influenza infection after study treatment, influenza severity, influenza treatment, influenza treatment outcome, date of recovery
Immune response	Seroconversion and seroprotection rates (GMT, GMR), influenza virus–specific memory A- and B-cell responses, confirmed influenza infection during follow-up
Adverse events	Dates, progress, intensity, expectability, causality, progress, toxicity degree
Concomitant treatments	Indication, dose, frequency, administration route, start and end dates

^a^COPD, Chronic obstructive pulmonary disease; GMR, Geometric mean ratio; GMT, Geometric mean titers.

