### Outcome measures

Seroconversion rate was the primary end-point variable of the study. Microneutralization assays were performed to quantify neutralizing antibody titers against the two influenza A strains and the influenza B strain. Immunological response and vaccination efficacy were based on the following international criteria: (1) geometric mean titers (GMT; mean antibody titer in the group of vaccinated individuals), (2) seroprotection rate (percentage of patients with antibody titers ≥1:40), (3) seroconversion rate (percentage of participants with four fold increase in antibody titers from baseline) and (4) geometric mean ratio (GMR; seroconversion factor postvaccination compared with prevaccination). Neutralizing antibody titers were evaluated at 5, 10 and 15 weeks and 1 year after influenza vaccination. Cellular immune response to vaccination was determined by quantifying influenza-specific CD4+ and CD8+ memory cells at baseline, 15 weeks and 1 year after influenza vaccination. For each treatment arm, clinical efficacy was assessed by evaluating the episodes of confirmed influenza infection during a 1-year follow-up period. The safety endpoints at each evaluation time frame were rejection episodes, hospitalization, graft loss, mortality, incidence of AEs and severe AEs and rates of discontinuation due to AEs.

In order to study in-depth the immune response to influenza vaccination in SOT recipients, we will also explore other genetic and biological outcomes in the collected samples. Genetic expression patterns of immune response and anti–human leukocyte antigen levels induced by influenza vaccination will be analyzed as ancillary outcomes.

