Efficacy analysis will be performed using seroconversion and seroprotection rates, GMT, GMR and incidence of confirmed influenza infection (to assess clinical effectiveness). The analysis will include, as covariates, previous influenza vaccination, previous record of confirmed influenza infection and other demographic and clinical variables. Additionally, a subgroup analysis will be performed to evaluate effectiveness in patients with decreased response to influenza vaccination (liver failure, use of mammalian target of rapamycin inhibitors, first 6 months posttransplantation).

Vaccination safety analysis will be performed using tabulations of AEs, and descriptive analysis will be provided at baseline and follow-up visits for each treatment group. A tabulation of SAEs will also be provided for each patient within each treatment group. The statistical analysis will be performed by treatment phase (up to 30 days after vaccination) and for the posttreatment phase (long-term follow-up), as appropriate. AEs will be classified on the basis of Medical Dictionary for Regulatory Activities (MedDRA) terminology and summarized for each treatment arm. AE incidence rates will be summarized by system organ class, preferred term, severity and relationship to the IMP. The proportion of patients in each treatment group reporting AEs that occur in ≥3% in each treatment group will be compared using Bayesian methods. The specific system organ classes and preferred terms analyzed will be those reported by at least 5% of the patients in each treatment group.

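### The T-cell comparison is not stated to adjust for each patient's measured baseline, which would gain precision at no cost; Table 3 also names a different cellular variable

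*Protocol article*

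**What the plan says.** One secondary objective, at the end of the Background, is to compare short-term and long-term influenza-specific T-cell responses between the arms.

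- **Read-out** (Methods/Design, text with Figure 1 under Follow-up protocol): "percentage of CD4+ and CD8+ T cells secreting interferon γ in response to influenza stimulation normalized to the negative control".
- **Timing** (Outcome measures): "Cellular immune response to vaccination was determined by quantifying influenza-specific CD4+ and CD8+ memory cells at baseline, 15 weeks and 1 year" after vaccination. Selection and enrollment confirms that blood is drawn before the first dose "for the quantification of baseline cellular and humoral immune response".
- **Analysis** (Statistical analysis): "Efficacy analysis will be performed using seroconversion and seroprotection rates, GMT, GMR and incidence of confirmed influenza infection"; the T-cell measure is not in this list. The covariates named there are earlier influenza vaccination, earlier confirmed influenza, and unspecified demographic and clinical variables. For quantitative variables the section gives Mann–Whitney or Student's t-test, with Welch if variances differ. It adds a multivariate model for possible confounders, without naming its terms.
- **Table 3**, immune response row: "influenza virus–specific memory A- and B-cell responses".

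For contrast, the primary antibody endpoint is tied to the patient's own starting value: "percentage of participants with four fold increase in antibody titers from baseline".

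**The concern.** Transplant recipients who have been vaccinated or infected before may carry influenza-specific T cells into the trial. A value at week 15 or 1 year therefore reflects both what the patient started with and what the vaccine added. Randomisation balances the starting level between arms on average, but differences between patients remain in the error term of an unadjusted test. The trial measures the quantity that would remove part of that noise and does not say that it will be used. The stake is a lower chance of detecting a real booster effect on cellular immunity.

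A smaller matter is that Table 3 names a cellular variable that does not match the T-cell outcome in the text. A reader cannot tell from the article whether B-cell responses are an outcome.

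**Working it through.** **1. The plan's own sample size.** Inputs from Sample size calculation: 77% versus 87%, two-sided 5%, 80% power, 1:1 allocation, 10% dropout. With the pooled-variance formula, where the mean of the two rates is 0.82:

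n = [1.960·√(2·0.82·0.18) + 0.842·√(0.77·0.23 + 0.87·0.13)]² / 0.10² = 230.5, rounded up to 231 per arm; 231/0.90 = 256.7, rounded up to 257.

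Both stated figures reproduce. They concern seroconversion. No SD, effect size or power is stated for the T-cell endpoint, so 231 per arm is used below only as the evaluable number, assuming that all these patients have cellular results.

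**2. Three ways to compare the arms.** Let r be the correlation between baseline and follow-up values on the analysis scale, with equal SDs. The variance of the arm difference, relative to a plain follow-up comparison, is:

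- follow-up value alone: 1
- change from baseline: 2(1 − r)
- follow-up adjusted for baseline (ANCOVA): 1 − r²

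The detectable difference in SD units is (1.960 + 0.842)·√(2v/231), where v is the relative variance. The article gives no r, so the values below are assumptions.

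| r | v, ANCOVA | variance removed | detectable, follow-up alone | detectable, change | detectable, ANCOVA | patients per arm for the same precision (231·v) |
|---|---|---|---|---|---|---|
| 0 | 1.00 | 0% | 0.261 | 0.369 | 0.261 | 231 |
| 0.3 | 0.91 | 9% | 0.261 | 0.308 | 0.249 | 210 |
| 0.5 | 0.75 | 25% | 0.261 | 0.261 | 0.226 | 173 |
| 0.7 | 0.51 | 49% | 0.261 | 0.202 | 0.186 | 118 |

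**3. Power for a true difference of 0.20 SD** (also an assumed value). Power = Φ(0.20/√(2v/231) − 1.960). This gives 57.5% unadjusted, and 61.5%, 69.9% and 85.3% adjusted at r = 0.3, 0.5 and 0.7.

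**4. ANCOVA against a change score.** 2(1 − r) − (1 − r²) = (1 − r)², which is never negative. ANCOVA is therefore at least as precise as a change score at every r, and as precise as the follow-up value alone even at r = 0. A change score beats the follow-up value alone only when r exceeds 0.5.

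**5. The cellular descriptions side by side.** The Figure 1 text has interferon-γ-secreting CD4+ and CD8+ T cells. Outcome measures has influenza-specific CD4+ and CD8+ memory cells. These can be the assay read-out and the population it identifies. Table 3 does not fit either: it names A- and B-cells and no T cells. If the A is a slip for T, B cells still appear nowhere else as an outcome and no B-cell assay is described.

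**The case against.** The strongest reply is that nothing in the article says only follow-up levels will be compared. Outcome measures includes baseline in how cellular response is determined. The multivariate model and the open-ended covariate list leave room for baseline T-cell level, and a condensed article may leave such detail to a full protocol or SAP. This stands as a limit on the point: adjustment may already be planned in a document not shown. It does not remove the point, because the article does name the two-group tests and some covariates, and this baseline value is not among them.

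Two stronger readings are tempting, and the documents do not support them.

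- A reader might infer that the T-cell endpoint fails to measure response to vaccination because it is referred only to the negative control. That normalisation is an assay step and is not restricted to post-vaccination samples. The arms are randomised, so comparing follow-up levels estimates the booster effect without bias. The article's own antibody criteria also include levels with no baseline term: GMT and the seroprotection rate.
- A reader might infer three competing definitions from which a result could be picked. Two of the three are compatible, as shown above; only the Table 3 entry clearly differs. That table is introduced as listing variables measured as appropriate at follow-up visits, so timing is not wholly absent for it either.

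It is also fair that the gain is conditional. At r = 0.3 it is slight, and at r = 0 there is none.

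**Conclusion.** The point holds as a modest improvement to a secondary analysis. The stated tests for a quantitative endpoint do not use a baseline value that the trial already collects. The cost is precision, not bias: 9% to 49% of error variance for r between 0.3 and 0.7, or a detectable difference of 0.25 to 0.19 SD instead of 0.26 SD. These figures rest on an assumed r, equal SDs, 231 patients per arm with T-cell data, and no adjustment being specified elsewhere. The proportion of variance removed does not depend on the number of patients.

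The Table 3 mismatch is real and largely editorial. Neither part touches the primary seroconversion comparison.

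**What to change.** - State that the arms are compared at week 15 and at 1 year by ANCOVA on the interferon-γ-secreting CD4+ and CD8+ percentages, each with the patient's own baseline value as covariate. Report the adjusted difference (or ratio, on a log scale) with its 95% CI.
- Fix the scale in advance. Percentages corrected for background can be zero or negative, depending on what normalised means here. A log analysis therefore needs a pre-set rule for such values; a rank-based ANCOVA avoids the need.
- Do not substitute a plain change score, which loses precision when r is below 0.5.
- Reconcile the Table 3 entry with the T-cell read-out in the Figure 1 text and Outcome measures. Check the full protocol before deleting the B-cell part. If B-cell response is an outcome, give its assay and time points; if not, correct the entry.

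The cost is wording and a few lines of analysis specification. No new sample or assay is needed, since the baseline cellular measurement is already part of the design. The article describes the analyses as still to come, so the specification should be settled before the T-cell data are compared by arm.
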